Biochemical markers of bone resorption and formation are inherently variable and only infer the metabolic state of bone turnover at the precise instance at which they are measured. Biochemical markers of bone resorption and formation often increase or decrease together and cannot be used to determine overall net bone mineral balance (*i.e.* whether bone resorption or bone formation is the prevailing process) [19]. Skulan and DePaolo (1999) [20] were the first to outline a conceptual model describing the fractionation of calcium isotopes between soft tissue and bone. Differences in isotopic composition between soft tissue and bone were reported, with bone being enriched with isotopically lighter calcium isotopes compared to soft tissue [20, 21]. Decreased BMD is associated with a net loss of calcium from the bone. Using the model formulated by Skulan and DePaolo (1999) [20], measuring changes in the natural calcium isotopic composition of calcium in the urine provides a non-invasive method to determine calcium homeostasis and calcium flux to, and from, bone [22–25]. Six, naturally occurring, stable calcium isotopes exist in the diet: ^40^Ca, ^42^Ca, ^43^Ca, ^44^Ca, ^46^Ca, and ^48^Ca. Bone formation favours the uptake of isotopically lighter calcium isotopes causing a shift in urine composition towards an isotopically heavier state [26]. When bone resorption is dominant, and calcium is lost from bone, the isotopic calcium composition of the urine becomes lighter [27]. Low calcium intake results in a negative bone calcium balance (*i.e.* calcium is derived from the skeleton to maintain serum calcium concentrations) [28], but the effects of military load carriage and calcium supplementation on bone calcium balance, determined from circulating and urinary calcium isotopes, is unknown.

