In the 24 h preceding each load carriage session participants will be rested (no exhaustive exercise) and will not apply skin moisturizer. Participants will arrive at the laboratory after an overnight fast, have an indwelling cannula inserted in a vein in the antecubital fossa, and a resting blood sample taken (Fig. 2). A calcium supplement (2 × 500 mg; Calcichew) will be given to each participant completing the Supplement condition ~ 60 min before starting the load carriage exercise [8]. Sweat collectors (Macroduct Sweat Collector, ELITech Group, France) [35] will be attached to the forearm for the measurement of sweat calcium excretion during exericse. A 120 min session of load carriage exercise will be completed. The load carriage exercise is a fitness test completed by the infantry. Participants will walk 12.8 km on the treadmill at 6.4 km·h^− 1^ for 120 min whilst wearing a 20 kg military backpack. Expired gases, heart rate, and rating of perceived exertion will be measured throughout the exercise. The first urine void upon waking (Fig. 2), and a urine void within ~ 1 h of the cessation of load carriage, will be obtained for the measurement of calcium isotopes for the calculation of bone calcium balance. Nude body mass will be measured before and immediately after exercise for the determination of sweat loss and calculation of sweat calcium excretion; post-exercise body mass will be adjusted for water consumed *ad libitum* during exercise. Calcium concentration of water consumed during exercise will be recorded. Blood samples will be taken at 0 min, and then every 20 min during, and 15, 30, 60, and 90 min following, load carriage. Blood samples fractioned into serum and plasma will be analysed for markers of bone formation, bone resorption, and calcium metabolism. Whole blood will be analysed immediately for blood lactate concentration (Lactate Pro 2, Arkray, Japan), ionized calcium, haemoglobin and haematocrit (i-STAT Alinity, Abbott, USA; CHEM8^+^, Abbott, USA) (Fig. 2). Isokinetic (60°·s^− 1^ and 180°·s^− 1^) and isometric (90° knee flexion) maximal voluntary contraction of the knee extensors and flexors (System 4, Biodex Medical Systems, USA) will be measured before and immediately after load carriage exercise. Researchers will monitor the laboratory testing procedures to ensure adhereance to study protocols; there is no criteria for the study to be discontinued.

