### Calcium isotope measurement in blood, urine, and sweat

Blood (serum), urine, and sweat samples will be analysed for total calcium and the stable calcium isotopes ^42^Ca and ^44^Ca as described elsewhere [24]. Urine (1 mL) and serum (0.25 mL) will be digested in 14 mol/L HNO_3_ and 2 mL of H_2_O_2_ (30%), then heated to 220 °C for 45 min and dried overnight at 120 °C. Dried samples will be dissolved in 2 mol/L HNO_3_ to reach a calcium concentration of 25 mg/L then undergo automatic chromatographic purification (prepFAST MC, ESI, USA); a solution almost solely containing calcium will be collected with a yield of more than 85%. Calcium solutions will be dried and treated at 120 °C for 3 h with 1 mL 14 mol/L, l HNO_3_ and 0.5 mL of H_2_O_2_ (30%), then dissolved in 0.2 mol/L HNO_3_ to yield a concentration of 2.5 mg/L. A maximum of 21 samples, one blank, and one of each reference material (NIST SRM 915a, IAPSO Standard Seawater, NIST SRM 1486), and one in-house standard for urine (AK-1) or serum (SERA-1) will be collected. Calcium isotope measurements will be performed on a Multicollector-Inductively Coupled Plasma-Mass Spectrometer (MC-ICP-MS) (Neptune plus, Thermo Fisher Scientific, Bremen, Germany). The mass spectrometer is equipped with nine Faraday cups of which eight are moveable. The mass spectrometer is set up to measure masses 42, 43, 43.5, and 44 simultaneously. To prevent interfering calcium and argon hybrids (*e.g. *^40^Ar^1^H_2_ on ^42^Ca) an APEX IR (ESI, Omaha, Nebraska, USA) sample introduction system is used. All measurements will be performed in medium resolution (MR, m/Δm ~ 4,000) on the interference-free plateau of the low mass side of the peaks, achieved by choosing an appropriate center cup mass of 43.687 ± 0.001 amu, verified on a daily basis (cf. [36]). Instrumental fractionation (mass bias) will be corrected by applying the standard-sample-bracketing approach. The measurement of a sample will be bracketed by measurements of a ~ 5 µg·mL calcium solution prepared from a 10,000 µg·g calcium ICP reference solution. Every sample will be measured at least four times during a session and the mean value used for further calculations. There is negligible isotope fractionation during purification (< 0.01‰) with this method. Although almost all strontium is removed from the samples during chemical preparation, samples will be monitored for doubly charged strontium (^84^Sr, ^86^Sr, and ^88^Sr) that can interfere with the measurement of ^42^Ca, ^43^Ca, and ^44^Ca (cf. [37]). Several criteria will be applied to reject data of a single measurement, a single sample, or a whole sequence [37]: a single sample will be rejected when |δ^44/42^Ca – 2·δ^43/42^Ca|>0.2‰; a single sample (4 or 5 single measurements) will be rejected when the average intensity is outside a 70 to 130% intensity window when compared to the average intensity of the reference solution from the same batch; a whole sequence will be rejected when more than one of the measured international reference materials deviates more than 0.2‰ from the literature value or the data will not fall along the mass-dependent fractionation line. The long-term 2-sigmal standard deviation reproducibility of the Ca isotope value is 0.06‰.

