### Statistical analyses

No previous studies have been published investigating calcium balance through natural calcium isotope ratios in response to exercise or calcium supplementation, therefore the required sample size for this study is calculated based upon data from high and low calcium diets to reflect the Control (no calcium) and Supplement (1000 mg calcium) conditions within this study. The required sample size was calculated in R (version 4.1.1) using the *‘pwr’* package based on testing the null hypothesis that there will be no difference in calcium balance between Control and Supplement conditions. Based on differences in calcium balance between women on a high (~ 1500 mg·d^− 1^) and low (~ 300 mg·d^− 1^) calcium diet (108.6 ± 127.9 vs. − 95.2 ± 24.6 mg·d^− 1^, d = 2.21) [28], and men on a low (376 mg·d^− 1^) and moderate (857 mg·d^− 1^) calcium diet (10.0 ± 6.0 vs. 0.1 ± 1.8 parts per ten thousand, d = 2.24) [22], it is anticipated that 5 people per group will be required to detect a difference in calcium balance between the Control group and Supplement group with an α of 0.05 and a 1 – ß of 0.90. The data from these trials were using chronic diets rather than acute supplementation and so we anticipate that the effect we will see will be much smaller. Therefore, a second sample size calculation was performed from PTH concentration (a secondary outcome) in response to exercise. Based on a 18.86 to 26.83 pg·mL^− 1^ [41–43] higher serum PTH during exercise without calcium supplementation compared with calcium supplementation (following a calcium meal [1352 ± 53 vs. 46 ± 7 mg [42]] or calcium drink [1000 mg·L^− 1^ [41]; 486 mg·L^− 1^ [43]), it is anticipated that 26 people will be required to detect a difference in serum PTH concentration (d = 0.667) between the Control group and Supplement group with an α of 0.05 and a 1 – ß of 0.90. A total sample of 30 will allow us to detect an effect of d ≥ 0.75 with an α of 0.01 and a 1 – ß of 0.90.

A per-protocol analysis will be performed. Significance will be accepted as p < 0.05.

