#### Primary outcomes

The absolute change in urine calcium balance (^44^Ca:^42^Ca) from pre- to post-load carriage will be compared between the Control condition and Supplement condition using a one-way analysis of covariance (ANCOVA) with pre-load carriage calcium balance (either as a ratio, or both the numerator and denominator) as the covariate. The minimal important difference in absolute change in urine calcium balance between the Control condition and Supplement condition is not known.

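### The calcium tablets can shift the primary urine isotope ratio directly, and the article describes neither a measurement of their ratio nor an allowance for it before a difference is read as bone balance

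*Protocol article*

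**What the plan says.** Background gives the reading of the endpoint: "measuring changes in the natural calcium isotopic composition of calcium in the urine provides a non-invasive method to determine calcium homeostasis and calcium flux". The flux meant is exchange with the skeleton. Heavier urine is taken as net formation and lighter urine as net resorption. The same section notes that these isotopes occur naturally in the diet. The stated hypothesis is that the supplement will prevent a negative calcium balance.

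Load carriage 1 and 2 fixes the dose and timing: "A calcium supplement (2 × 500 mg; Calcichew) will be given to each participant completing the Supplement condition". This is 1000 mg in total, taken about 60 min ahead of the 120 min walk. The baseline urine is "The first urine void upon waking", so it precedes the tablets. The second urine, within about an hour "of the cessation of load carriage, will be obtained for the measurement of calcium isotopes for the calculation of bone calcium balance", follows them.

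The section on calcium isotope measurement lists what is assayed: "Blood (serum), urine, and sweat samples will be analysed for total calcium and the stable calcium isotopes" 42Ca and 44Ca. The tablets are not in that list.

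Under Primary outcomes, the absolute change in the urine ratio "will be compared between the Control condition and Supplement condition using a one-way analysis of covariance (ANCOVA") with the pre-exercise value as covariate. Neither that model nor the delta formula in Data analyses contains a term for ingested calcium. Primary outcomes also says that no minimal important difference is available.

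**The concern.** The treatment is itself a source of the isotopes that form the endpoint. Absorbed tablet calcium enters serum, and from there urine, carrying whatever 44Ca/42Ca ratio the tablets have. If that ratio differs from the body pool, the urine ratio moves in the Supplement condition even when calcium flux to and from bone is the same in both conditions. The shift could look like a bone effect or cancel a real one, depending on its sign.

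The features that normally protect a crossover do not help here:

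- Randomisation and crossover cannot separate the two, because the tablet is the contrast being tested.
- The ANCOVA covariate is measured before the tablets.
- More participants make the combined effect more precise without splitting it.
- The serum ratio at 120 min has received the same absorbed calcium.
- The cited diet studies offer no direct reassurance. Statistical analyses itself says "The data from these trials were using chronic diets rather than acute supplementation", so they concern a different situation from a few hours after one dose.

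At stake is the conclusion drawn from the primary outcome. The comparison of ratios remains valid as a comparison; its attribution to bone may not.

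**Working it through.** **The plan's own figure.** Statistical analyses says that 30 women can detect d ≥ 0.75 at α = 0.01 with 90% power. A two-sided paired t test with n = 30 and d = 0.75 gives power 0.902, so the figure reproduces. The point here concerns what the contrast means and does not change the sample size.

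**Timing (Load carriage 1 and 2).** Tablets to post-exercise void: 60 + 120 + (0 to 60) min = 180 to 240 min, or 3–4 h. Tablets to baseline void: the void comes first.

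**Size of the shift.** With bone balance identical in both conditions, two-source mixing gives

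shift = f × D,

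where f is the share of post-exercise urinary calcium that came from the tablets and D is the tablet δ44/42Ca minus the body-pool δ44/42Ca. Neither is in the documents, so both are assumptions.

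- *f*: absorbed / (absorbed + exchangeable pool). With 100 mg absorbed and a 2000 mg pool, 100/2100 = 0.048. With 200 mg and 1000 mg, 200/1200 = 0.167. With 300 mg and 1000 mg, 300/1300 = 0.231. The extreme corner, 300 mg into 500 mg, is 300/800 = 0.375. The working range is 0.05–0.30.
- *D*: 0 to 1.0‰, either sign. Zero belongs in the range because the tablets may match the body pool.

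| D (‰) | shift at f = 0.05 | shift at f = 0.30 |
|---|---|---|
| 0 | 0 | 0 |
| 0.3 | 0.015 | 0.09 |
| 0.5 | 0.025 | 0.15 |
| 1.0 | 0.05 | 0.30 |

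**Noise.** The isotope measurement section gives a 2-SD reproducibility of 0.06‰, so the SD per value is 0.03‰. SD of a change = 0.03 × √2 = 0.042‰. SD of the difference between two changes = 0.042 × √2 = 0.06‰. This contains assay error only and is therefore a floor. Values of 0.12 and 0.20‰ are assumed to allow for variation within women.

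**Chance of p < 0.05 with no bone effect.** Two-sided paired t, n = 30, 29 degrees of freedom, noncentrality = (shift/SD) × √30. This stands in for the planned ANCOVA.

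| Shift (‰) | Example | SD 0.06 | SD 0.12 | SD 0.20 |
|---|---|---|---|---|
| 0.005 | f = 0.05, D = 0.1 | 7% | 6% | 5% |
| 0.03 | f = 0.10, D = 0.3 | 75% | 26% | 13% |
| 0.10 | f = 0.20, D = 0.5 | >99% | 99% | 75% |

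For the second row at SD 0.06, the noncentrality is (0.03/0.06) × √30 = 2.74. The smallest shift is close to the nominal 5%, and the largest would usually be declared significant.

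**A rough scale from the plan.** The chronic-diet isotope contrast quoted in Statistical analyses is 10.0 − 0.1 = 9.9 parts per ten thousand, or 0.99‰ (isotope pair not stated there). The plan expects the acute effect to be much smaller, so shifts in the upper part of the table above need not be small beside it.

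**The case against.** The strongest reply is that the size is wholly assumed. Nothing in the article gives the tablet ratio, the body-pool ratio, the amount absorbed or the pool size. If the tablets match the body pool there is no artefact. That stands, and it is why the range starts at zero. It also means that the direction of any bias is unknown.

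Second, the noise may be larger than assay error. A reader might divide the shift by the assay-only standard error, 0.06/√30 = 0.011‰, and infer that even a 0.03‰ artefact would dominate the trial. The documents do not support that, because variation within women is left out. At an SD of 0.20‰ the same shift reaches significance in only 13% of trials.

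Third, the mixing model is simple. A void collects urine since the bladder was last emptied, and the article does not time that emptying, so the average tablet share could be below the end-point value. This argues for a range of f rather than a single figure.

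Fourth, the article is condensed and refers to cited sources for its isotope procedures. A reader might infer that the tablets will not be measured at all. Only the weaker statement is supported: no such measurement is described. The listed sample types, the delta formula and the analysis nevertheless leave no place for the ingested ratio, and that is part of the stated interpretation rather than laboratory detail.

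Two further inferences should be resisted. Drinking water is not a comparable problem: it is taken freely in both conditions and its calcium concentration is recorded. Nor would the serum ratio at 120 min permit a full mass-balance correction, since absorbed tablet calcium and bone flux both act on it and remain two unknowns.

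**Conclusion.** The concern holds as a limit on interpretation. The planned comparison of urine ratios is valid as a comparison, but the article gives no basis for assigning a Control–Supplement difference to bone while the tablets' own ratio is left out. Under the assumed f of 0.05–0.30 and D of 0–1.0‰ in either direction, the spurious shift runs from nothing to about 0.30‰. Whether it matters depends on D, which can be measured, and on f, which can only be bounded. A reader might go further and infer that a significant primary result would be an artefact. The documents do not show that; they show only that such a result could not be told apart from one.

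**What to change.** 1. Use a single tablet batch for all participants, and measure δ44/42Ca in a few tablets by the MC-ICP-MS procedure already planned.
2. State in Primary outcomes a prespecified range for f, with its reasoning, and the resulting range of f × D with its sign. State that a Control–Supplement difference will be attributed to bone calcium balance only if it exceeds that shift throughout the range. Where the tablet shift runs opposite to the observed or expected effect, report the difference less f × D across the same range, so that masking is visible.
3. If the tablet ratio matches the body pool, say so; no adjustment is then needed.

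The cost is a handful of extra assays on an instrument in use and a short paragraph. Sample size, visits and sampling do not change. The downside is that the bone-balance claim becomes conditional on the assumed range of f.

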### Biological sample collection and storage

Venous blood samples will be drawn into vacutainers for the collection of serum (SST II Advance serum separator, and silica, Becton Dickinson, USA) and plasma (K2EDTA, Becton Dickinson, USA). Serum and plasma vacutainers will stand at room temperature for 30 min before centrifugation at 3000 *g* 4 °C for 10 min. Serum and plasma fractions will be stored at −80 °C until analysis. Venous blood samples for the collection of whole blood will be drawn into a lithium heparin vacutainer (Becton Dickinson, USA), analysed immediately and then disposed of. Urine voids will be collected into a 1 L container; a 10 mL volume will be aspirarted into a Monovette (Sarstedt, UK) containing boric acid and stored at −80 °C until analysis. Sweat samples will be transferred to 1.5 mL microvettes and stored at −80 °C until analysis.

### Calcium isotope measurement in blood, urine, and sweat

Blood (serum), urine, and sweat samples will be analysed for total calcium and the stable calcium isotopes ^42^Ca and ^44^Ca as described elsewhere [24]. Urine (1 mL) and serum (0.25 mL) will be digested in 14 mol/L HNO_3_ and 2 mL of H_2_O_2_ (30%), then heated to 220 °C for 45 min and dried overnight at 120 °C. Dried samples will be dissolved in 2 mol/L HNO_3_ to reach a calcium concentration of 25 mg/L then undergo automatic chromatographic purification (prepFAST MC, ESI, USA); a solution almost solely containing calcium will be collected with a yield of more than 85%. Calcium solutions will be dried and treated at 120 °C for 3 h with 1 mL 14 mol/L, l HNO_3_ and 0.5 mL of H_2_O_2_ (30%), then dissolved in 0.2 mol/L HNO_3_ to yield a concentration of 2.5 mg/L. A maximum of 21 samples, one blank, and one of each reference material (NIST SRM 915a, IAPSO Standard Seawater, NIST SRM 1486), and one in-house standard for urine (AK-1) or serum (SERA-1) will be collected. Calcium isotope measurements will be performed on a Multicollector-Inductively Coupled Plasma-Mass Spectrometer (MC-ICP-MS) (Neptune plus, Thermo Fisher Scientific, Bremen, Germany). The mass spectrometer is equipped with nine Faraday cups of which eight are moveable. The mass spectrometer is set up to measure masses 42, 43, 43.5, and 44 simultaneously. To prevent interfering calcium and argon hybrids (*e.g. *^40^Ar^1^H_2_ on ^42^Ca) an APEX IR (ESI, Omaha, Nebraska, USA) sample introduction system is used. All measurements will be performed in medium resolution (MR, m/Δm ~ 4,000) on the interference-free plateau of the low mass side of the peaks, achieved by choosing an appropriate center cup mass of 43.687 ± 0.001 amu, verified on a daily basis (cf. [36]). Instrumental fractionation (mass bias) will be corrected by applying the standard-sample-bracketing approach. The measurement of a sample will be bracketed by measurements of a ~ 5 µg·mL calcium solution prepared from a 10,000 µg·g calcium ICP reference solution. Every sample will be measured at least four times during a session and the mean value used for further calculations. There is negligible isotope fractionation during purification (< 0.01‰) with this method. Although almost all strontium is removed from the samples during chemical preparation, samples will be monitored for doubly charged strontium (^84^Sr, ^86^Sr, and ^88^Sr) that can interfere with the measurement of ^42^Ca, ^43^Ca, and ^44^Ca (cf. [37]). Several criteria will be applied to reject data of a single measurement, a single sample, or a whole sequence [37]: a single sample will be rejected when |δ^44/42^Ca – 2·δ^43/42^Ca|>0.2‰; a single sample (4 or 5 single measurements) will be rejected when the average intensity is outside a 70 to 130% intensity window when compared to the average intensity of the reference solution from the same batch; a whole sequence will be rejected when more than one of the measured international reference materials deviates more than 0.2‰ from the literature value or the data will not fall along the mass-dependent fractionation line. The long-term 2-sigmal standard deviation reproducibility of the Ca isotope value is 0.06‰.

### Biochemical markers of bone formation and bone resorption

Pre-screen and load carriage (Fig. 2) blood sample analysis will be performed at the Bioanalytical Facility, University of East Anglia (Norwich, UK) by the COBAS automated platform (Roche Diagnostics, Mannheim, Germany). Procollagen type 1 N-terminal propeptide, (P1NP), iPTH, beta carboxy-terminal cross-linking telopeptide of type 1 collagen (βCTX) and osteocalcin will be analysed in EDTA plasma, whereas albumin-adjusted calcium, phosphate, luteinising hormone, follicle stimulating hormone, oestradiol, and sex hormone binding globulin in serum. Sample analysis will be carried out according to manufacturers’ instructions and under Good Clinical and Laboratory Practice conditions. The inter-assay coefficient of variations (CV) are ≤ 3% within their respective analytical working range. LC-MS/MS will be used to measure serum testosterone, 25(OH)D3, 25(OH)D2, 24,25-dihydroxyvitamin D3 (24,25(OH)_2_D3), 24,25-dihydroxyvitamin D2 (24,25(OH)_2_D2), 1,25-dihydroxyvitamin D3 (1,25(OH)_2_D3), and 1,25-dihydroxyvitamin D2 (1,25(OH)_2_D2), with their respective vitamin D metabolite ratio [38]. The measurement ranges of the assays are: 0–25 nmol/L for 24,25(OH)_2_D2 and 24,25(OH)_2_D3, and 15–600 pmol/L for 1,25(OH)_2_D2 and 1,25(OH)_2_D3. The mean CV for intra-assay imprecision across the measuring range of the assays are: ≤ 7.7% for 24,25(OH)_2_D2, 9.0% for 24,25(OH)_2_D3, and ≤ 7.4% for 1,25(OH)_2_D. The cumulative inter-assay CVs are: ≤ 10.6% for 24,25(OH)_2_D2, ≤ 8.9% for 24,25(OH)_2_D3, and ≤ 9.3% for 1,25(OH)_2_D. Plate-based enzyme-linked immunosorbent assay (ELISA) will be used to analyse for bone-specific alkaline phosphatase (bone ALP) (MicroVue, Quidel, San Diego, CA, USA) and sclerostin (Biomedica, Vienna, Austria) in serum. Inter-assay CV for bone ALP is ≤ 5.8%, and  < 8.5% for sclerostin.

